### Safety monitoring

Patients will be followed up by a multidisciplinary team at three time points: study start, week 4, and week 8. Possible complications will be assessed by the study cardiologist and pharmacist. The safety assessment will consist of monitoring adverse events, such as changes in the digestive tract, physical exams, and laboratory tests. Events, onset, and duration will be reported to the cardiologist, who will determine if it is necessary to suspend supplement use. Regular intake of omega-3 PUFAs is not a risk to health. According to the US Food and Drug Administration (FDA), the maximum intake of 3 g/day EPA + DHA is considered safe [51].

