## Methods/Design

### Study design

This is a parallel, double-blind, placebo-controlled clinical trial with balanced randomization (1:1).

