### Procedures, follow-up, and data collection

After patients are selected by cardiologists, they will be seen by study nutritionists, who will explain the study procedures to the patients and administer the free and informed consent form. The patients who agree to participate in the study will sign the consent form and undergo the initial assessment.

The following data will be collected and evaluated in the study: sociodemographic data (age, sex, ethnicity/race, education, and domicile), clinical data (functional class and vital signs), alcoholism, smoking, prescription drugs, 3-day food record [48], 24-h recall [49], anthropometric assessment (height, weight, BMI, waist circumference, tricipital skinfold thickness, and arm circumference), lipid profile (total cholesterol, triglycerides, HDL-c, LDL-c, and VLDL-c), and cytokines (IL-1, IL-2, IL-4, IL-6, IL-10, TNFα, IFNγ, and TGFβ). Clinical, nutritional, and anthropometric assessments will take place immediately before starting the intervention and after 4 and 8 weeks during the study; lipid profile and cytokines will be evaluated before the intervention and at the end of 8 weeks. Each patient will be followed for 8 weeks.

Compliance with study treatment will be assessed by the 3-day treatment recall and the number of omega-3/placebo capsules returned. At every visit, the patients will be asked about the number of doses of the prescribed treatment that they did not take during the previous 3 days, and the ratio between the number of doses taken and the number prescribed will be calculated. The capsules will be dispensed at the beginning of the study and after 4 weeks, and the returned capsules will be verified at weeks 4 and 8.

The dietary omega-3 PUFA intake will be followed-up during the study (first visit and weeks 4 and 8) by analyzing the 24-h recall and 3-day food record, which are considered indirect methods of analyzing the diet, current dietary standards of a certain population, and their development over time [50].

Patients may be excluded from the study in case of complications during follow-up, such as significant changes in intestinal transit, use of anti-inflammatory drugs, and hospital admissions. Other complications will be assessed by the study team. All endpoints will be collected at time 0 and 8 weeks after omega-3/placebo supplementation starts.

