### Randomization and concealment

After the screening phase, patients will be randomly assigned to 1 of 2 groups of 20 patients each: intervention group or control group. Assignment to either group will be performed by a computer-generated 1:1 randomization. This assignment will occur within randomly ordered blocks of size 4 or 6. This procedure will be conducted using R project software with package 'blockrand’ [52].

The allocation sequence will be concealed from the researchers, who will enroll and assess participants in sequentially numbered, opaque, sealed, stapled envelopes. To prevent subversion of the allocation sequence, the name and date of birth of the participant will be written on the envelope before the envelope is opened. The information in the envelope will be transferred onto the allocation card inside the envelope. Corresponding envelopes will be opened only after the enrolled participants have completed all baseline assessments and at the time of allocation to the intervention. These procedures will be carried out by a professional without access to the baseline evaluation results. The blister packaging and gel capsules of omega-3 PUFAs and placebo will be identical. They will be identified by the lot number on the package, which will be retained in the pharmacy, and only the blisters will be provided to patients. The pharmacist responsible for distribution and compliance assessment will be the only person who can access this information.

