### Blinding

The nutritionists and physician that will perform the initial evaluation before randomization, the monthly evaluations and anthropometric profile, and the final evaluation of the health care questionnaires after the end of the patient follow-up will be blinded to the patients’ assignments.

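### The pharmacist who alone can identify the treatment also helps assess complications that may lead to exclusion, so knowledge of allocation can influence who is excluded

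*Protocol article*

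**What the plan says.** The Abstract and Study design both call the trial double-blind. Four later sections of the protocol article assign the roles that matter here.

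- **Randomization and concealment**, on the omega-3 and placebo packs: "They will be identified by the lot number on the package, which will be retained in the pharmacy, and only the blisters will be provided". On access to that identification: "The pharmacist responsible for distribution and compliance assessment will be the only person who can access this information".
- **Safety monitoring:** "Possible complications will be assessed by the study cardiologist and pharmacist". The same section adds: "Events, onset, and duration will be reported to the cardiologist, who will determine if it is necessary to suspend supplement use".
- **Procedures, follow-up, and data collection:** "Patients may be excluded from the study in case of complications during follow-up, such as significant changes in intestinal transit". The other grounds named are admission to hospital and taking anti-inflammatory drugs. On anything else: "Other complications will be assessed by the study team".
- **Blinding:** the nutritionists and physician who carry out the evaluations "will be blinded to the patients’ assignments". The pharmacist is not listed.

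Cytokines, the primary endpoint, are measured before treatment and at 8 weeks. Each arm has 20 patients.

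**The concern.** The one person named as having access to the treatment identity is also given a share in assessing events that can take a patient out of the study. Exclusion is discretionary, and a significant change in intestinal transit has no stated threshold, so it is a matter of judgement. Digestive-tract changes are also the example of an adverse event given under Safety monitoring. The Background mentions gastrointestinal effects in some omega-3 studies, though without a difference from placebo. Someone who knows the arm could still read the same complaint differently in the two groups.

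The stake is selective loss. A patient excluded before week 8 may contribute no post-baseline cytokine value, and a blinded, objective assay cannot repair a selected set of patients. With 20 per arm, a few such decisions carry weight.

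**Working it through.** **Step 1. Setting the roles side by side.**

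| Task | Who, according to the article | Stated to be blinded? |
|---|---|---|
| Access to the lot identification | Pharmacist only | No |
| Dispensing and compliance assessment | Same pharmacist | No |
| Assessing possible complications | Study cardiologist and pharmacist | Cardiologist: only if this is the physician under Blinding, which is not stated. Pharmacist: no |
| Assessing other complications | Study team, not specified further | Not stated |
| Deciding on suspension of the supplement | Cardiologist | As above |
| Deciding on exclusion | Nobody named | Not stated |

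The article does not say outright that the pharmacist under Safety monitoring is the one under Randomization and concealment, but it describes no other. On that reading, the path from known allocation to exclusion runs through the joint assessment of complications. Nothing in the text closes it.

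**Step 2. Weight of one exclusion.** 1/20 = 5% of an arm.

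**Step 3. A worst-case scale.** The article states no bias figure, so there is none to reproduce. Everything in this step except the arm size is an assumption: a normal outcome, no true effect, and exclusion of exactly the highest-ranking patients on a variable that correlates r with the outcome.

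If the k highest of 20 are removed, the mean of the remainder falls by (sum of the k largest expected normal order statistics)/(20 − k), in SD:

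- 5 removed: 6.07/15 = 0.405 SD
- 2 removed: 3.28/18 = 0.182 SD
- difference between arms, 5 versus 2: 0.405 − 0.182 = 0.223 SD

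The bias in the outcome is 0.223 × r:

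| r | Bias (SD) |
|---|---|
| 0 | 0 |
| 0.1 | 0.02 |
| 0.2 | 0.04 |
| 0.5 | 0.11 |
| 0.8 | 0.18 |

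**Step 4. Effect on the false-positive rate.** A simulation of 200,000 trials with 20 per arm used a two-sided t test at 0.05. It removed the highest outcome values themselves (r = 1) from one arm only:

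| Removed from one arm | Shift in mean (SD) | Type I error |
|---|---|---|
| 1 | 0.10 | 6.8% |
| 2 | 0.18 | 10.0% |
| 3 | 0.26 | 14.5% |

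**Step 5. Comparison with the planned effect.** From the sample size section, the IFNγ difference is 3,986 − 2,922 = 1,064 pg/mL. The pooled SD is √((738² + 1,275²)/2) = 1,042 pg/mL, so the planned effect is 1,064/1,042 = 1.02 SD. A bias of 0.18 SD is 0.18/1.02, or about 18% of that effect. This is small beside the effect planned for, but Step 4 shows that shifts of this size can raise the false-positive rate.

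**The case against.** The strongest defence is that the safeguards that matter most are in place. Capsules and blisters are identical, the staff who evaluate patients are blinded, and the primary endpoint is a serum assay run in triplicate. No section gives the pharmacist access to cytokine results. An unblinded pharmacist at the dispensing end is compatible with a double-blind trial. Hospital admission and anti-inflammatory drug use leave little room for judgement. All of this stands, and it limits the concern to intestinal transit and the unspecified other complications.

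Three stronger readings are tempting, and the article does not support them.

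- **That the pharmacist can decide who is excluded.** The only decision-maker named under Safety monitoring is the cardiologist, and that decision is about suspending the supplement. No one is named for exclusion. The text supports influence through a joint assessment and no more.
- **That unblinded compliance grading affects who stays in the analysis.** No section ties compliance to exclusion, to an analysis set or to an endpoint. Compliance is a capsule count and a ratio of doses taken to doses prescribed.
- **That a bias of 0.11 to 0.18 SD is to be expected.** Those values need perfect selection of extremes, 5 versus 2 exclusions, and correlations of 0.5 to 0.8. The article supports none of these. Blinded exclusions driven by a real difference in tolerability would give the same figure, so it does not measure the effect of unblinding.

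It can also be said that a condensed article leaves role details to the full protocol. That would answer an omission. Here the article itself assigns the two roles that conflict.

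**Conclusion.** The point holds in a limited form. The person with sole access to the treatment identity shares in assessing complications, complications can lead to discretionary exclusion, and no section says that exclusion is judged blind. Knowledge of allocation can therefore influence who reaches the week 8 measurement. It is not shown that it decides this, or that any bias has occurred.

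The firm figure is 5% of an arm per exclusion. The bias figures, from nil to about 0.18 SD over correlations of 0 to 0.8, are an assumed worst case for scale only. The conclusion rests on one pharmacist filling both roles. It leaves open whether the study cardiologist is the blinded physician. The change should be made because it closes a route to bias at almost no cost.

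**What to change.** Reconcile the sections on procedures, safety monitoring, concealment and blinding by adding three statements:

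1. Complications, for the purpose of exclusion, and every exclusion decision are judged only by staff blinded to allocation.
2. The study cardiologist is among the blinded staff.
3. The pharmacist who holds the code takes no part in exclusion decisions.

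The pharmacist can keep dispensing and the count of returned capsules. No dose, visit, safety procedure or rule on suspending the supplement needs to change. The cost is a few sentences and a small reassignment of existing tasks to existing staff.

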### Randomization and concealment

After the screening phase, patients will be randomly assigned to 1 of 2 groups of 20 patients each: intervention group or control group. Assignment to either group will be performed by a computer-generated 1:1 randomization. This assignment will occur within randomly ordered blocks of size 4 or 6. This procedure will be conducted using R project software with package 'blockrand’ [52].

The allocation sequence will be concealed from the researchers, who will enroll and assess participants in sequentially numbered, opaque, sealed, stapled envelopes. To prevent subversion of the allocation sequence, the name and date of birth of the participant will be written on the envelope before the envelope is opened. The information in the envelope will be transferred onto the allocation card inside the envelope. Corresponding envelopes will be opened only after the enrolled participants have completed all baseline assessments and at the time of allocation to the intervention. These procedures will be carried out by a professional without access to the baseline evaluation results. The blister packaging and gel capsules of omega-3 PUFAs and placebo will be identical. They will be identified by the lot number on the package, which will be retained in the pharmacy, and only the blisters will be provided to patients. The pharmacist responsible for distribution and compliance assessment will be the only person who can access this information.

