### Participants (inclusion and exclusion criteria)

Patients will be recruited from the cardiology ambulatory service at IPEC/Fiocruz, Rio de Janeiro, Brazil, during the period determined for screening until the minimum estimated sample size is reached. All patients had a previous epidemiologic history of Chagas disease confirmed with at least two Chagas serology tests (indirect immunofluorescence and ELISA), and clinical evaluations, electrocardiographic and echocardiographic data obtained recently. Selected patients will be older than 18 years, males and females with CCC at stage B (no heart failure symptoms but with segmental or global left ventricular systolic dysfunction by echocardiogram), stage C (symptomatic heart failure), or stage D (end-stage heart failure), according to the current Brazilian Chagas disease consensus [3]. The following exclusion criteria will be applied: diarrheal disease; inflammatory bowel syndrome; diagnosis of diabetes or other endocrine pathologies; use of fibrates, niacin, or statins; use of anti-inflammatory drugs; pregnant and lactating women; vitamin mineral or omega-3 supplementation during the previous 30 days; hospital admission during the study; and the presence of cardiomyopathies other than CCC.

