A clinical trial evaluated 3-month omega-3 PUFA supplementation in patients with heart failure. Patients were divided into three groups: placebo, 1 g/day omega-3 PUFAs, and 4 g/day omega-3 PUFAs. Only the 4 g/day group had an improvement in ventricular function with an increase in the ejection fraction and endothelial function and a reduction in IL-6 [36]. We will use 3 g/day omega-3 PUFAs in our study based on recent results suggesting higher efficacy when compared to the usual 1 g dose, in addition to the fact that 3 g/day is considered safe by the FDA [51]. According to a recent American College of Cardiology and American Heart Association (ACC/AHA) Heart Failure Guideline, omega-3 supplementation is reasonable to use as adjunctive therapy in heart failure patients (Class of Recommendation IIa, Level of Evidence B ) [62].

The worse prognosis and progression of CCC are related to increased immune response with the production of proinflammatory cytokines and the inhibition of anti-inflammatory cytokines, which also occur in other cardiomyopathies [63,64]. In Chagas disease, heart tissue is an important target of *T. cruzi* infection, and substantial amounts of proinflammatory cytokines, chemokines, and enzymes, including inducible nitric oxide synthase and metalloproteinases, are produced, resulting in inflammation and cardiac remodeling in response to parasite infection [65]. Higher levels of IFNγ and TNFα are associated with lower levels of IL-4 and IL-10, in both cardiac and more severe forms of Chagas disease, and high levels of IL-10 or moderate levels of IFNγ are associated with the indeterminate form [15,66]. Omega-3 and omega-6 PUFA intake may lead to an increase in IL-10 production, as shown in an experimental study in Wistar rats supplemented with ethyl-eicosapentaenoic acid and ethyl-γ-linolenic acid compared to a group supplemented with palm oil [67]. Thus, omega-3 PUFA supplementation in CCC patients may lead to increased IL-4 and IL-10, reducing the inflammatory effect on heart tissue.

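### Disease stages B, C and D are pooled in 40 patients with neither stratification by stage nor adjustment for it, which costs precision on the cytokine endpoint though not validity

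*Protocol article*

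**What the plan says.** All places are in the protocol article.

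- **Participants (inclusion and exclusion criteria).** "Selected patients will be older than 18 years, males and females with CCC at stage B" (no heart failure symptoms, but left ventricular systolic dysfunction), "stage C (symptomatic heart failure), or stage D (end-stage heart failure), according to the current Brazilian Chagas disease consensus". No cap or expected share per stage is given.
- **Randomization and concealment.** Patients are "randomly assigned to 1 of 2 groups of 20 patients each: intervention group or control group". "This assignment will occur within randomly ordered blocks of size 4 or 6". There is one series of numbered envelopes, and no stratification factor is named.
- **Statistical methods.** Numerical variables are compared between the two groups by Student's t test, or by the Wilcoxon test if not normally distributed. No covariate is named.
- **Discussion.** "The worse prognosis and progression of CCC are related to increased immune response with the production of proinflammatory cytokines". It adds: "Higher levels of IFNγ and TNFα are associated with lower levels of IL-4 and IL-10, in both cardiac and more severe forms of Chagas disease". The same sentence sets this against the indeterminate form of the disease.
- **Procedures, follow-up, and data collection.** Cytokines are measured before the intervention and at 8 weeks.

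**The concern.** Eligibility runs from patients without heart failure symptoms to patients with end-stage heart failure. If cytokine levels rise or fall with severity inside that range, stage adds variance to the primary endpoint that has nothing to do with omega-3. Blocks of 4 or 6 balance the total numbers, not stage, and 20 per arm is small enough for sizeable chance differences. The stated test leaves the between-stage variance in the error term. It also has no means of correcting the estimate if the single allocation that this trial will have turns out uneven.

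**Working it through.** **1. Inputs and the plan's own figure.** From Minimum sample size estimation: IFNγ 3,986 (SD 738) and 2,922 (SD 1,275) pg/mL, power 0.8, α 5% (taken as two-sided).

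- Difference = 3,986 − 2,922 = 1,064.
- Pooled SD = √((738² + 1,275²)/2) = 1,042.
- Standardised effect = 1,064/1,042 = 1.02.
- n per arm = (738² + 1,275²)(1.96 + 0.842)²/1,064² = 15.05, rounded up to 16, so 32 in total (34 by the exact t test).

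The stated 40 is not reproduced. That is a separate matter and does not bear on this point. At 20 per arm the exact t-test power is 88.2%.

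**2. Chance imbalance in stage.** The stage mix is not given, so it is assumed. With K stage C/D patients among 40, the number in one arm is hypergeometric (40, K, 20).

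| K (C/D of 40) | P(arms differ by ≥4) | P(arms differ by ≥6) |
|---|---|---|
| 10 | 27% | 6% |
| 14 | 32% | 10% |
| 20 | 34% | 11% |

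For K = 20, a difference of 4 is a 12 v 8 split.

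**3. What one such allocation does.** Shift in the arm difference = (difference in C/D share) × (stage gap). A difference of 4 patients is 4/20 = 0.20.

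| Assumed gap, C/D v B | Shift, gap scaled on SD 1,042 | Shift, gap scaled on baseline SD 738 |
|---|---|---|
| 0.5 SD | 0.20 × 521 = 104 pg/mL (10% of 1,064) | 0.20 × 369 = 74 pg/mL (7%) |
| 1 SD | 0.20 × 1,042 = 208 pg/mL (20%) | 0.20 × 738 = 148 pg/mL (14%) |

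The standard error of the arm difference is 1,042 × √(2/20) = 329 pg/mL. Even 208 is only 208/329 = 0.63 of a standard error.

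**4. What adjusting for stage (B v C/D) does to power.** Take K = 20 and hold the total SD at 1,042.

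- Stage explains a share p(1 − p)g² of the variance, with p = 0.5 and g the gap in SDs.
- The residual SD is 1,042 × √(1 − share).
- The residual degrees of freedom fall from 38 to 37.
- The treatment variance is inflated by 1/(1 − r²), where r is the arm-stage correlation. Under chance allocation r² averages 1/39. Power is averaged over the hypergeometric splits.

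| Gap g | Residual SD | Power, unadjusted | Power, stage-adjusted |
|---|---|---|---|
| 0 | 1,042 | 88.2% | 87.3% |
| 0.25 | 1,034 | 88.2% | 87.8% |
| 0.5 | 1,009 | 88.2% | 89.3% |
| 1 | 902 | 88.2% | 94.7% |

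**5. Is stratification needed as well?** A simulation (4,000 runs per cell) used an assumed B/C/D mix of 50/35/15% and a gap per stage step of 0.25, 0.5 or 0.75 SD.

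| Design and analysis | Type I error | Power |
|---|---|---|
| Unstratified, unadjusted (as planned) | 4.4, 5.2, 4.7% | 88.6, 87.5, 87.8% |
| Stratified, unadjusted | 4.3, 3.6, 2.6% | 88.6, 88.6, 91.5% |
| Unstratified, stage-adjusted | 5.1, 5.0, 4.7% | 88.6, 91.6, 95.2% |
| Stratified, stage-adjusted | 4.6, 5.9, 5.2% | 89.3, 92.3, 95.9% |

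Stratifying on top of adjustment adds 0.7 points in each case. Stratifying while keeping the unadjusted test gains 0 to 4 points and makes the test conservative.

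**The case against.** Unstratified permuted blocks are a valid and common choice for a 40-patient single-site trial. Over repeated allocations the estimate is unbiased, chance imbalance is already inside the 5% error rate, and power at 20 per arm exceeds the planned 80% on the protocol's own inputs. Covariates are often left to an analysis plan, which is not shown here. All of this stands, and it makes the point one of efficiency. It does not remove it, because the article names the test it will use, and that test ignores a factor known for every patient at entry.

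A reader might go further in four ways that the document does not support.

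- **That the protocol itself says stages B, C and D have different cytokine levels.** Its explicit contrast is with the indeterminate form, which is not eligible. Only the general statement on CCC progression points to a gradient within CCC, and that gradient remains an inference.
- **That imbalance biases the trial or inflates false positives.** The simulated type I error for the plan as written is 4.4-5.2%. Mimicking or masking an effect describes one unlucky draw.
- **That BMI and waist comparisons are distorted too.** Nothing links stage to these measures, and the Background says that the nutritional assessment of CCC patients has not been reported.
- **That allocation should be restarted on stage-specific lists.** Recruitment is open (Trial status), so new lists might balance few patients. The envelopes are also handled by someone without access to baseline results, who would then have to know the stage.

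**Conclusion.** The point holds as a loss of precision that is cheap to recover, not as an error in the randomisation. With 10 to 20 stage C/D patients among 40, about 27-34% of allocations leave the arms four or more such patients apart, and the stated analysis has no term for it. One such allocation would move the IFNγ difference by about 7-20% of the planned 1,064 pg/mL, if the stage gap is 0.5 to 1 SD. Adjusting for stage would raise power by about 1 to 7 points over the same gaps when half the patients are C/D. At a gap of 0.25 SD or less it gains nothing and costs up to 0.9 points.

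The stage mix and the stage gap are both assumptions, since the article gives neither. If cytokines do not vary by stage within CCC, nothing is lost under the present plan except the ability to show it.

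**What to change.** In Statistical methods, replace the unadjusted primary comparison with a linear model (ANCOVA) for each cytokine: week-8 value on treatment, stage (B v C/D) and the baseline value of that cytokine, on a transformed scale such as the logarithm if skewed. Fix the model, the stage grouping and the choice of scale before unblinding. Record stage at entry as an analysis variable; eligibility already requires it to be known. If a separate analysis plan already contains such a model, bring the article's statement into line with it.

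The cost is one residual degree of freedom per covariate. For stage this is just under 1 point of power (88.2% to 87.3%) if it is not prognostic. The baseline cytokine needs no new data. With an assumed within-arm baseline to week-8 correlation of 0.3, 0.5 or 0.7, it multiplies the residual SD by √(1 − r²) = 0.95, 0.87 or 0.71.

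Leave the allocation lists as they are, because adjustment alone recovers most of the gain.
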